**Strength**					
Weeks 1–2	3	10	60% 1RM	3 sets * 10 reps * 60 kg	1800
Weeks 3–4	3	10	65% 1RM	3 sets * 10 reps * 65 kg	1950
Weeks 5–6	3	10	70% 1RM	3 sets * 10 reps * 70 kg	2100
Weeks 7–8	3	10	75% 1RM	3 sets * 10 reps * 75 kg	2250
**Endurance**					
Weeks 1–2	3	20	30% 1RM	3 sets * 20 reps * 30 kg	1800
Weeks 3–4	3	20	35% 1RM	3 sets * 20 reps * 35 kg	2100
Weeks 5–6	3	20	40% 1RM	3 sets * 20 reps * 40 kg	2400
Weeks 7–8	3	20	45% 1RM	3 sets * 20 reps * 45 kg	2700

RM: repetition maximum.

To guarantee safety, tolerability will be assessed in each session using a numerical rating scale for pain (NRS, scale 0–10) or, where appropriate, physical examination. For NRS > 5, training load is modified. PTs may provide tailored instructions during sessions, following the same procedure for both groups.

The home-based exercises are initially taught at Reade and consist of bodyweight and resistance bands exercises. Exercise selection is the same across groups. However, the strength group uses bands with greater resistance. Additionally, repetition counts and rest intervals mirror those used in supervised sessions. Patients are instructed to target an intensity of 7–8 on a 10-point physical exertion scale. To ensure adherence to the intended intensity level, patients are asked to be aware of effort using easily measurable physiological indicators such as breathing rate, perspiration, and muscle soreness. Exercises are regularly evaluated and adjusted as needed by the treating physiotherapist.

#### Additional intervention.

As part of regular clinical care all patients will receive two one-hour educational sessions from an occupational therapist on improving their capacity, the balance between physical and mental load, and joint-protection. Where indicated by the supervising rehabilitation physician, participants may also receive psycho-education, support from a social worker, or podiatry.

### Outcome measures

Fig 1 lists all descriptive data, primary and secondary outcomes, and other measures (e.g., treatment adherence and process measures).

The primary outcome is isokinetic muscle strength (*peak torque)* assessed using an isokinetic dynamometer Biodex System (Enknee Enraf-Nonius, the Netherlands)). **Peak torque** will be measured in both upper legs using knee extension test. Participants will first perform a familiarization trial. Subsequently, they will complete three maximal-effort repetitions at an angular velocity of 60°/s to assess the isokinetic strength of the quadriceps for each leg. The average torque (in Newton-meters, Nm) produced by the quadriceps per leg will be calculated and normalized to body weight (Nm/kg). For analysis, values from the index knee (i.e., the most affected knee) will be used [36]. In addition to absolute peak torque (Nm), relative muscle force will be assessed by calculating torque relative to physiological cross-sectional area (PCSA) as derived from 3D ultrasound (Nm/cm^2^). This provides an indication of muscle quality (i.e., force-generating capacity per unit muscle area).

Measurements will be performed at the start and end of the exercise intervention (except the muscle biopsy, which will be only taken prior to the intervention).

Secondary outcome measures include muscle endurance, and i) muscle morphology, (ii) mitochondrial function, and (iii) systemic inflammation (see Table 4). These parameters will be assessed using the Six minute Walk test (6MWT), an isokinetic dynamometer, 3D ultrasound (3D US), high-resolution respirometry (HRR), and blood-based biomarker analysis (Multiplex/ELISA), respectively and will be described in detail.

**Table 4 pone.0356181.t004:** Overview of secondary outcome measures, examples of measurements, related pathways relevant to the C4M study and the techniques to be applied.

Secondary Outcome Measure	Examples of read-outs	Related Pathway relevant to C4M	Technique to be applied
(i) **Muscle morphology**	• muscle belly length (ℓm); muscle fascicle length (ℓfasc); physiological cross-sectional area (PCSA); tendon length (ℓt); and muscle-tendon complex length (ℓm + t)	Muscle plasticity	3DUS
(ii) **Muscle mitochondrial function**	• Basal respiration; Leak respiration; NADH-linked respiration, Succinate-linked respiration, Maximal Oxidative Capacity; Maximum uncoupled respiration	Energy production (/ oxidative capacity)	high-resolution respirometry
**iii) Blood biomarkers**	• IL-6; IFN-γ; IL-17; IL2; IL-4; IL-10 and TNF-α	Systemic inflammation	Multiplex/ ELISA

Muscle endurance: The 6MWT will be used to measure functional endurance. Participants are instructed to walk as far as possible along a 30-meter walkway for six minutes. The total distance covered (meters) will be recorded as an indicator of functional endurance [37]. Muscle specific endurance will be assessed by using an isokinetic dynamometer Biodex System**®**, using the same setup as for peak torque. Resistance will be set at 40–60% of the participant’s average peak torque to ensure submaximal loading. Participants will perform repeated concentric knee extensions until torque output drops by 15% from the initial 40–60% level. The total number of repetitions completed before this decline is recorded.

i) Muscle morphology: 3D US (Affiniti 30 Ultrasound system of Philips, Bothell US) of the vastus lateralis muscle of the index knee will be used to quantify volume, muscle belly length (ℓm), muscle fascicle length (ℓfasc), physiological cross-sectional area (PCSA), tendon length (ℓt), and muscle-tendon complex length (ℓm + t) [38] of the vastus lateralis. Muscle volume is measured between the origin and distal end of the muscle belly using manual segmentation of the anatomical cross-sections and interpolation in custom software. Average fascicle length (ℓfasc) and pennation angles (αfasc) are estimated. A pennation angle is the angle between the longitudinal axis of the entire muscle and its fibers. PCSA is calculated by dividing muscle volume by ℓfasc.ii) Mitochondrial function: HRR will be used to measure mitochondrial energy production (i.e., mitochondrial oxidative capacity) with the Oxygraph-2k high-resolution respirometer (Oroboros Instruments, Innsbruck, Austria), [39]. In brief, mitochondrial function will be assessed with permeabilized muscle fibers originating from the muscle biopsy. The biopsy will be performed at the mid-section of the vastus lateralis of the quadricep muscle under local anesthesia (2–3 mL of 1% xylocaine), using a Bergström needle modified for manual suction. A small incision (~1 cm) will be made through which the biopsy is retrieved, and closed with skin glue or, if needed, sutures (Donati stitch). Part of the biopsy will be mechanically separated under a microscope to expose individual muscle fibers, followed by gentle teasing with fine forceps to improve substrate accessibility. This physical permeabilization step ensures that the sarcolemma is disrupted while preserving mitochondrial structure and function, allowing direct measurement of mitochondrial respiration using the Oxygraph system. Fibers will be transferred to the Oxygraph chambers and mitochondrial oxygen consumption will be continuously measured while performing a substrate-inhibitor-uncoupler-titration protocol. This protocol involves sequential addition of glutamate, malate, and pyruvate to assess complex I supported leak respiration, followed by ADP to stimulate coupled oxidative phosphorylation (OXPHOS) via complex I (NADH-linked), cytochrome *c* to test for outer mitochondrial membrane integrity, succinate to assess complex II supported respiration (Succinate-linked), FCCP to reveal total uncoupled electron transport system (ETS) capacity, rotenone to inhibit complex I, and finally antimycin A to inhibit complex III and reveal residual oxygen consumption. Systemic inflammation: blood will be withdrawn for investigation of blood-biomarkers for systemic inflammation (IL-6; IFN-γ; IL-17; IL-2; IL-4; IL-10 and TNF-α). Serum will be sampled from all participants and analyzed with multiplex cytokine analysis or ELISA (BD™ Cytometric Bead Array (CBA) Human Th1/Th2/Th17 CBA Kit, BD Biosciences, San Jose, CA, USA) to identify the cytokines that are differentially expressed in the RA, OA, and SARC patients. The following general inflammation markers will be assessed in addition to that: C-reactive protein (CRP) and erythrocyte sedimentation rate (ESR).

Other measures: To enable in-depth characterization of the study participants the following variables will be collected.

a. Patient characteristics: Sociodemographic and lifestyle characteristics will be assessed using a standardized questionnaire, including age, gender, height, weight, educational level, employment status, marital status, smoking and alcohol use (including duration), symptoms, and use of walking devices. Comorbidity will be assessed using the Cumulative Illness Rating Scale (CIRS) [40], administered through a semi-structured interview. Information on current medication use will be obtained from the participant’s medical record. Protein intake will be assessed using a 24-h dietary recall conducted by a trained researcher. Protein intake (g/day) will be calculated using the Netherlands Nutrition Centre database.b. Anthropometrics: Body composition will be assessed using direct-segmental multi-frequency bio-electrical impedance analysis (DSM-BIA) (Biospace Co, Korea). DSM-BIA has been validated for assessing segmental and whole-body composition against dual energy X-ray absorptiometry (DXA) [41]. Muscle mass is expressed as SMM (kg), SMM index (SMI, kg/m^2^) by dividing SMM (kg) by height squared (m^2^) [30], relative SMM (%) by dividing SMM (kg) by body weight (kg)*100, ALM/height^2^ (kg/m^2^) by dividing ALM (kg) by height squared (m^2^) and fat free mass (%).c. Disease characteristics: diagnosis will be obtained from the participant’s medical record; Radiologic severity of osteoarthritis will be assessed using Kellgren and Lawrence grade (K&L) [42].d. Performance: handgrip strength will be assessed with a JAMAR**®** Dynometer (Patterson Medical, UK) [43,44]. Participants will be seated with elbows flexed at 90 degrees, shoulders adducted and forearms in a neutral position without support. They will be instructed to squeeze the dynamometer maximally three times per hand, alternating between the right and left sides. The highest recorded value (kg) will be reported; Short Physical Performance Battery (SPPB test) [45]. The SPPB assesses lower extremity function through three components i) Balance Test: Participants perform progressively challenging standing positions (feet together, semi-tandem, and full tandem stance) for up to 10 seconds each. ii) Gait Speed Test: Walking speed is measured over a 4-meter course. iii) Chair Stand Test: Participants complete five timed chair rises without using their arms for support. The time to complete the five repetitions will be recorded in seconds. The total SPPB score (0–12) reflects overall lower limb function, with higher scores indicating better performance.e. Patient-Reported Outcome Measures (PROMs) will be measured with online questionnaires: Numeric Rating scale pain (0–10) [46], PROMIS® short forms regarding fatigue (8a) version 1.0, physical function (8b) version 2.0, ability to participate in social roles and activities (8a) version 2.0 [47]. FitMáx© survey [48] is a questionnaire consisting of three single answer questions, about the maximum capacity of walking (scale from 0–13), climbing stairs (scale 0–10) and cycling (scale 0–11). By adding the participant’s sex, age and BMI, the FitMáx© model estimates the maximum oxygen uptake, expressed in ml/kg/min [48,49].

EuroQol- 5 Dimension (EQ5D) questionnaire is used to assess five domains (mobility, self-care, usual activities, pain/discomfort, anxiety/depression) and includes a visual analogue scale (VAS) for self-rated health status [50].

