**Methods:**

This two-arm, parallel-group exploratory trial will enroll 69 patients (23 RA, 23 OA, 23 SARC), randomized to endurance (n = 35) or muscle strength exercises (n = 34), using minimization to balance disease type and gender. The 8-week intervention includes two supervised sessions per week using a controlled cable pulley device (Reforter™) and fitness equipment, plus one weekly home-based session. The primary outcome is isokinetic muscle strength (peak torque), measured with the Biodex system**®**. Secondary outcomes include muscle morphology, mitochondrial function, systemic inflammation and muscle endurance (by Biodex and 6 Minute Walk test). Muscle morphology will be assessed via 3D ultrasound imaging of the vastus lateralis. Mitochondrial function will be analyzed using high-resolution respirometry on muscle biopsies. Systemic inflammation will be measured using multiplex assays or ELISA on serum samples.

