**Fig 2 pone.0356181.g002:**
[figure not shown]
Overview trial logistics: Participants with RA, OA, or SARC are recruited and screened for eligibility. After informed consent (IC), they are randomized (minimization) to the endurance or strength exercise group. Baseline assessments (T0, week 0) include biopsy, performance tests, blood, questionnaires, imaging, and isokinetic muscle strength measures. The exercise program starts within a maximum of 2 weeks after baseline assessment. After an 8-week supervised intervention, follow-up assessments (T2, week 9) repeat all baseline measures except the biopsy.

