#### 2. Secondary outcome (Associations between muscle characteristics and exercise response).

i) Linear regression analyses will be conducted for each characteristic, e.g., muscle morphology (marker: DSM-BIA, physiological cross-sectional area and pennation angle), mitochondrial function (marker: Basal respiration; Leak respiration; NADH-linked respiration, Succinate-linked respiration, Maximal Oxidative Capacity; Maximum uncoupled respiration), and inflammation (markers: IL-6; IFN-γ; IL-17; IL2; IL-4; IL-10 and TNF-α). The change in muscle strength (T1 – T0) will be the dependent variable, and each muscle characteristic will serve as the independent variable.ii) To explore whether associations between muscle characteristics and exercise response differ by exercise modality, models will be extended by including exercise group and interaction terms (muscle characteristic × exercise group). Given the exploratory nature of the study and the limited sample size, these analyses are intended to identify potential signals rather than provide definitive evidence of effect modification. Interaction estimates will be interpreted cautiously, with emphasis on estimated effect sizes and 95% confidence intervals rather than statistical significance testing.iii) Adjusting for covariates. All models will be adjusted for the minimization factors (gender and disease type) and prespecified covariates (age and BMI). Given the exploratory nature of the study and the available sample size, the number of covariates will be restricted to reduce the risk of model overfitting..iv) Aforementioned steps will be repeated with other clinical outcomes (isokinetic muscle endurance, 6MWT, SPPB physical function and pain) as the dependent variables to address the secondary objective of the study.

Missing data will be addressed using the Multivariate Imputation by Chained Equations (MICE) method when data were assumed to be Missing Completely at Random (MCAR) or Missing at Random (MAR). Variables with substantial missingness (>30%) or data deemed Missing Not at Random (MNAR) will be excluded. Analyses on imputed data will be compared with the original dataset to assess consistency.

Analyses will be based on the intention-to-treat principle (ITT), in which data of all participants will be analyzed according to group assignment. In addition, per-protocol analysis will be performed including only those participants that performed 80% or more sessions.

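### The secondary analysis does not match the listed secondary outcomes: one is measured only at baseline, two appear only as predictors, and endurance has no designated arm contrast

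*Protocol article*

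**What the plan says.** The abstract and the Outcome measures section agree on the list. The abstract has "Secondary outcomes include muscle morphology, mitochondrial function, systemic inflammation and muscle endurance", and Outcome measures has "Secondary outcome measures include muscle endurance, and i) muscle morphology, (ii) mitochondrial function, and (iii) systemic inflammation". Table 4 repeats morphology, mitochondrial function and blood biomarkers under the column for secondary outcome measures.

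On timing, Outcome measures schedules everything at the start and end of the programme, "except the muscle biopsy, which will be only taken prior to the intervention". The Fig 2 caption says the same: "follow-up assessments (T2, week 9) repeat all baseline measures except the biopsy". On the source of the mitochondrial data: "mitochondrial function will be assessed with permeabilized muscle fibers originating from the muscle biopsy".

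On analysis, Data analysis plan section 1 specifies a linear mixed model with a time × exercise group term, written for muscle strength only. Section 2, headed as the secondary outcome, has four steps. Step i: "The change in muscle strength (T1 – T0) will be the dependent variable, and each muscle characteristic will serve as the independent variable". Step ii adds exercise group and a characteristic × exercise group interaction. Step iii adds covariates. Step iv: "Aforementioned steps will be repeated with other clinical outcomes (isokinetic muscle endurance, 6MWT, SPPB physical function and pain) as the dependent variables".

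**The concern.** The first stated aim is to compare the effects of the two exercise types, and the trial is also meant to supply effect sizes for later studies. A reader of the outcome list will therefore expect an estimated arm difference for each secondary outcome. The section carrying that heading instead sets out a prediction and effect-modification analysis. The label and the analytic role differ for three of the four domains. For the fourth, the arm term that exists is not the quantity the aim calls for.

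Two things are at stake. Mitochondrial function could be reported as an outcome although the design holds no post-training value. And the arm differences in endurance, morphology and inflammation, for which the data will be collected, could be left undefined or read off a coefficient that depends on how a covariate is scaled.

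**Working it through.** The plan gives no figure to reproduce on this point. The check sets each domain's measurement times beside its role in the analysis.

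| Domain | Measured | Role in section 2 | Between-arm contrast stated |
|---|---|---|---|
| Mitochondrial function (6 respirometry read-outs in Table 4) | Baseline only | Independent variable | None possible |
| Muscle morphology | Baseline and follow-up | Independent variable | None |
| Systemic inflammation | Baseline and follow-up | Independent variable | None |
| Muscle endurance (Biodex repetitions, 6MWT) | Baseline and follow-up | Dependent variable (step iv) | Exercise group, only with an interaction (step ii) |

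**Mitochondrial function.** A between-arm effect needs a value after randomised treatment. Respirometry needs biopsy tissue, and follow-up repeats everything but the biopsy. With one time point there is neither a change nor a post-training comparison, whatever model is chosen.

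**Morphology and inflammation.** Step i puts them on the right-hand side. Step iv changes the dependent variable to endurance, 6MWT, SPPB and pain, and does not include them. The time × group term of section 1 is written for strength.

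**Muscle endurance.** Combining steps ii and iv, and leaving out covariates, the model is

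change in endurance = a + b·group + c·X + d·(group × X) + error,

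where X is one muscle characteristic. Here b is the arm difference at X = 0. If the arm difference at the mean of X is δ and the mean of X is m (in SD units, with d per SD), then

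b = δ − d·m.

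So b equals δ when X is centred (m = 0) or when there is no interaction (d = 0). The article does not say whether X is centred. For a quantity such as PCSA, zero lies outside anything that can be observed.

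**Illustration.** The documents give no effect size or SD, so these inputs are assumptions: δ = 0.5, d = 0.3 per SD, main slope 0.2, residual SD 1. The group size of 30 per arm is the number the article expects to analyse. There were 4,000 simulated trials.

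| Mean of X above zero | b by formula | b simulated (mean SE) | Plain arm contrast (mean SE) |
|---|---|---|---|
| 0 SD (centred) | 0.5 − 0.3×0 = 0.50 | 0.50 (0.26) | 0.50 (0.27) |
| 2 SD | 0.5 − 0.3×2 = −0.10 | −0.10 (0.60) | 0.50 (0.27) |
| 4 SD | 0.5 − 0.3×4 = −0.70 | −0.71 (1.11) | 0.49 (0.28) |

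Under these assumptions the coefficient changes sign and loses precision through scaling alone, while the plain contrast stays near 0.5.

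**The case against.** The strongest reply has four parts.

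First, arm terms are planned. Steps ii and iv together put exercise group into the models for Biodex endurance and 6MWT. This stands. A reader might infer that the plan contains no between-arm estimate for any secondary outcome, or that the trial could not speak to endurance at all; the text does not support either.

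Second, centring is a coding detail that an analysis plan may settle, and with centring the coefficient is the average arm difference (0.50 in the illustration). This also stands. A reader might infer that none of the group coefficients could be the arm effect, but that assumes uncentred coding, which the article does not state. Nor can the number of such coefficients be counted from the text, because the characteristics are introduced as examples and body composition alone yields several measures.

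Third, the baseline-only biopsy is disclosed in two places, and the mitochondrial data are used in the way an association aim requires. That is fair: the analysis of these data is coherent, and no sentence expressly promises a training effect on them. The error lies in calling them an outcome.

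Fourth, a condensed article may leave secondary contrasts to a fuller document. This would answer a complaint about silence. But the article is not silent: it fixes an analysis under the secondary-outcome heading, and that analysis does not fit the list. No other document can supply a follow-up biopsy under this schedule. One could also read step iv as reaching back to the primary model, but it sits under section 2 after steps i to iii, and its list of dependent variables would still leave out morphology and inflammation.

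**Conclusion.** The point holds as a mismatch between outcome labels, measurement times and analytic roles. One of four listed domains has no post-training value, so an exercise effect on it cannot be estimated. Two are measured twice but are used only as predictors. One has an arm term that is conditional on a characteristic and is not designated as the overall effect.

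The first two statements rest on the text alone. The third rests on the ordinary meaning of a main-effect coefficient in an interaction model; how far it departs from the average arm effect depends on coding and on the size of the interaction, neither of which is known. The illustrative figures show what can happen and do not forecast this trial. The primary analysis and the sample size are not affected.

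**What to change.** 1. For each secondary outcome measured twice (6MWT, Biodex repetitions, the chosen morphology read-outs, the cytokines), fit the section 1 model with time × exercise group, disease type and gender, or an equivalent baseline-adjusted model. Report the arm difference with a 95% CI, labelled exploratory.
2. State whether morphology and inflammation are predictors, outcomes or both.
3. Centre the muscle characteristics in the step ii interaction models, and say so.
4. In the abstract, Outcome measures and Table 4, relabel mitochondrial function as a baseline predictor or candidate effect modifier, and state that the trial cannot estimate an effect of either exercise type on it.

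The cost is a few more exploratory models, and more estimates to report and interpret with restraint. No visit, procedure or participant is added.
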